Fundamental differences do exist between the CBT and PEP interventions. CBT is a theoretically-based therapy that focuses on the role that cognitive processes play in the maintenance of problem behaviours, mood states, and habits [58]. CBT also highlights the relationship between thoughts, feelings and actions, and utilizes techniques involving motivation, goal-setting, problem-solving, and knowledge/skill acquisition that can facilitate sustainable behaviour changes [59]. This intervention is designed to promote parental adoption of a more authoritative parenting style, which is exemplified by elements including rational decision-making, verbal give-and-take, autonomous self-will, and disciplined conformity. CBT can improve parenting style and parent–child interactions [60], so group leaders work with parents who have more permissive (e.g., makes few demands) or authoritarian (e.g., restricts child autonomy) parenting approaches to help them to develop authoritative parenting skills. The skills learned in CBT help parents to identify and change the parenting mechanisms that maintain their children’s current lifestyle habits; group leaders help parents to link knowledge, attitudes, thoughts, and feelings to behaviours and facilitate setting incremental goals that build on one another week-to-week in a manner that corresponds to parent motivation. CBT encourages consistent participation and collaboration between group leaders and participants; a Socratic questioning approach is also applied to help parents find their own answers to problems instead of having questions answered or problem-solved by group leaders [61]. To ensure the CBT-based version adhered to the main tenets of cognitive behavioural interventions, we consulted an international, three-member panel of clinical and research experts in CBT, obesity, and intervention development and evaluation. Their critical evaluation, feedback, and recommendations for revisions were incorporated into the curriculum.

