In contrast, PEP is a knowledge-based intervention that is modeled after traditional nutrition and health education programs. Information regarding healthier parenting styles is provided in a didactic manner without directive leader-initiated goal-setting or problem-solving. In relation to CBT, PEP is a more passive intervention and there is limited focus on active skill building. The intervention is predicated on a more traditional approach that assumes behaviour change results from increased knowledge, although different activities are included for parents that encourage learning (individual activities, brain-storming, hands-on experiential learning) [62]. While group discussions and problem-solving are included within PEP, active integration of learned concepts in goal-setting and linking cognitions and behaviours to lifestyle changes are not integral. There is no active cognitive or behavioural skill building process embedded in the program. In relation to CBT, PEP requires less investment of energy and participation from parents, which many parents prefer. While PEP does not represent a true control group, its content and delivery are consistent with what many clinicians provide for weight management.

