#### Family enrolment, intervention dose, and attrition

The study research coordinator record several study-specific variables that will be used to populate the CONSORT diagram (Figure 1). For instance, the total number of families recruited and enrolled in the study, parent attendance at each of the PAC sessions, and time of and reason for dropping out of the study are all documented.

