### Randomization

Parents are randomly assigned to either the CBT-based or PEP-based PAC intervention group following their completion of pre-intervention assessments, but before the initiation of the PAC sessions. Given that parents and their children are recruited and enrolled into the group-based interventions in several cohorts, we use a computer-generated, block randomization approach, which is completed by one of our research team members who has no direct contact with participants. Parents will be blinded to group assignment, and while they are aware that there are two groups of parents receiving the PAC intervention, they are unaware of the modality and methodological differences between CBT and PEP.

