### Statistical analysis

Data cleaning, analyses, figures, tables, and statistical sections for dissemination are conducted by a blinded biostatistician with the Biostatistics Consulting Group within the Women and Children’s Health Research Institute (http://www.wchri.org) at the University of Alberta. Spotfire S + 8.2 (TIBCO Software Inc, 2010) and SAS 9.3 (SAS Institute Inc, 2010) will be used for analyses. Analyses are conducted both with PAC intervention completers only and with all participants (to evaluate effectiveness). Continuous variables are described by summaries (e.g., means, medians, ranges and SDs) and frequency distributions are determined for categorical variables. For the primary and secondary outcome variables, the percent change from pre- to post-intervention (as well as 6- and 12-months follow-up) for both groups is determined and summarized along with the 95% confidence intervals (CIs) for mean percent change. Boxplots and histograms are used to display the percent change for these variables; bar charts are used for categorical variables. Our analyses are conducted separately for each mean percent change at each observation time (i.e., pre-intervention to post-intervention, pre-intervention to 6-month follow-up, and pre-intervention to 12-month follow-up). Statistical tests are set at conventional levels (p < 0.05) and all analyses are intention-to-treat. Multiple imputation methods may be used in the event of missing data. To minimize the risk of bias, a research team member with no direct contact with enrolled families is leading the data analyses.

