To compare interventions, one-sided independent samples Student’s t-test assesses percent changes in BMI z-score (primary objective); if required, data transformations are used to ensure data normality. A similar process is used to determine intervention-mediated changes in other physiological, behavioural, and psychosocial outcomes (secondary objectives). In addition, the percentage of families with improved categorical outcomes (i.e., those who do/do not meet recommendations from *Eating Healthy with Canada’s Food Guide*) is compared across interventions using a one-sided independent samples proportion tests. A multivariable linear regression model is developed for the primary outcome (percent change in BMI z-score) to determine the intervention group effect while controlling for potential confounders (i.e., cohort, percent attendance, household income). If any of the intervention groups include siblings, CIs are adjusted using variance inflation factors, and univariable or multivariable random intercept mixed effects models are used in lieu of Student’s t-tests and multivariable linear regression, respectively. Analogous calculations are made to compare the percent change from pre-intervention to 12-month follow-up, although intervention attrition may reduce our power to detect a significant difference. Mixed effect models are developed to examine the effects of the interventions on primary and secondary outcomes over time. This approach allows all pre-intervention, post-intervention, and follow-up data to be included in our modeling. For all models, residual diagnostics are used to assess model assumptions and appropriate transformations and/or non-linear terms are included as necessary. Our reporting of study results is in accordance with the CONSORT statement [91].

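### The supporting regression on the primary outcome adjusts for percent attendance, a post-randomisation variable, so its arm coefficient need not be the effect of assignment

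*Protocol article*

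**What the plan says.** The Statistical analysis section assigns the primary objective to an unadjusted one-sided t-test on percent change in BMI z-score. It then adds a multivariable linear regression on the same outcome, whose purpose is to estimate the arm effect while "controlling for potential confounders (i.e., cohort, percent attendance, household income". If siblings enrol, random-intercept mixed models replace both the t-test and the regression. The same section states that "all analyses are intention-to-treat".

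The Sample size section gives the regression its own power statement: 80% power at the 0.05 level to detect an R² of 10% for the intervention, with five control variables explaining 20% of the variability. The five are not named.

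On timing, the Randomization section places allocation "following their completion of pre-intervention assessments, but before the initiation of the PAC sessions". The section on enrolment, intervention dose and attrition says that the coordinator documents "parent attendance at each of the PAC sessions".

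The section comparing the two versions describes different demands on parents. For one arm, "CBT encourages consistent participation and collaboration between group leaders and participants". For the other, "PEP requires less investment of energy and participation from parents, which many parents prefer".

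**The concern.** A confounder of a randomised comparison would have to be related to allocation other than as its consequence. Cohort and household income are fixed before allocation and are ordinary covariates. Percent attendance is produced afterwards, by parents who have already experienced one of the two programmes.

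Holding it fixed does two things. It removes whatever part of the programme's effect works through getting parents to come. It also compares parents with equal attendance in two programmes that may have demanded different effort. If the arm shifts attendance, those parents need not be alike in motivation, and motivation may itself affect the child's outcome.

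Nothing in the article labels this model as a dose, mediation or per-protocol analysis; its stated aim is the arm effect. A reader would therefore take the adjusted coefficient as a refined estimate of the effect of assignment. With about 30 families per arm analysed, an adjusted result that disagreed with the t-test would be hard to interpret.

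**Working it through.** **1. The plan's own figure.** Inputs from the Sample size section: N = 60, five controls with R² = 0.20, added R² = 0.10 for the intervention, alpha 0.05.

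- f² = 0.10 / (1 - 0.20 - 0.10) = 0.1429
- degrees of freedom 1 and 60 - 1 - 5 - 1 = 53; noncentrality 60 × 0.1429 = 8.57
- power = 0.82, against the stated 80%

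The figure is reproduced if the 10% is read as R² added to the 20%. This is therefore a planned and powered model.

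**2. Order of events.** Baseline assessment, then randomisation, then the sessions at which attendance is counted. All of percent attendance lies after allocation.

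**3. General result.** In a linear model with arm and attendance (other covariates left out for simplicity):

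adjusted arm coefficient = total effect - s × D

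Here D is mean attendance in CBT minus mean attendance in PEP, and s is the within-arm slope of outcome on attendance. The bias is -s × D. It is zero if D = 0 or s = 0. The article gives neither quantity, so all inputs below are assumptions. Negative values mean a fall in BMI z-score.

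**4. If CBT lowers attendance, with no true effect.** Assume that motivation shifts attendance by 0.15 (15 points) per SD and BMI z-score change by -k per SD, with residual attendance SD 0.15 and no direct effect of attendance.

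- s = -k × 0.15 / (0.15² + 0.15²) = -k × 3.33
- k = 0.2 gives s = -0.667; k = 0.3 gives s = -1.0

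| D | k = 0.2 | k = 0.3 |
|---|---|---|
| -0.10 | -0.067 | -0.100 |
| -0.20 | -0.133 | -0.200 |

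The table shows the adjusted coefficient when the truth is zero: a false CBT benefit of about 0.07 to 0.20 z.

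**5. If CBT raises attendance, with a true total effect of -0.50.** Put attendance in within-arm SD units. Let a be the arm's effect on attendance, b the direct effect of attendance on outcome, g the effect of motivation on outcome, and c = 0.5 the effect of motivation on attendance. Then s = b + g × c, and the adjusted coefficient is -0.50 - a × (b + 0.5g).

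| a | b | g | s | adjusted |
|---|---|---|---|---|
| 0 | any | any | b + 0.5g | -0.50 |
| 0.25 | -0.15 | 0 | -0.15 | -0.4625 |
| 0.50 | 0 | -0.3 | -0.15 | -0.425 |
| 0.50 | -0.3 | 0 | -0.30 | -0.35 |
| 0.50 | -0.3 | -0.3 | -0.45 | -0.275 |
| 0.75 | -0.3 | -0.3 | -0.45 | -0.1625 |

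Simulation with 400,000 records per scenario agreed with the formula to within 0.01. Where the arm shifts attendance, a true -0.50 shrinks to between about -0.46 and -0.16. Without attendance in the model, the coefficient is -0.50 in every row. With the sign of a reversed, the benefit would be exaggerated instead.

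**6. Scale.** The planned model uses percent change in BMI z-score; steps 4 and 5 use absolute z units. They show the mechanism and a plausible order of size, not a forecast.

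**The case against.** The strongest objection is that this is not the primary test. The unadjusted t-test contains no attendance term. That stands: a reader might infer that the primary result is biased, and the article does not support this.

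A second objection is that bias is conditional. Both arms have 16 sessions of the same length and format, every family must have a parent who agrees to attend weekly, and parents are not told how the programmes differ. The sentence about PEP requiring less participation may concern effort within sessions rather than session counts. This also stands in part. A reader might infer that attendance is expected to differ by arm, or to be lower in CBT. The article says neither, and its descriptions of the two arms point in opposite directions. A difference nevertheless remains plausible, because parents who do not know the modality still experience its demands.

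Third, adjusting for attendance moves nobody between arms and excludes nobody, so a flat contradiction of intention-to-treat would be too strong a reading. What remains is that the coefficient is no longer guaranteed to be the total effect of assignment, which is what that principle is there to protect.

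Finally, the sizes are assumed. At a 10-point attendance gap the false benefit of 0.07 to 0.10 z is under half of one standard error of the difference (0.83 × √(2/30) = 0.21). That is fair as to size, but it does not make attendance a confounder.

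**Conclusion.** The point holds for the supporting regression and its mixed-model version. The article names percent attendance as a confounder in a model meant to estimate the arm effect, although attendance arises wholly after randomisation. The coefficient departs from the effect of assignment if two things are true together: the arm changes attendance, and attendance is related to outcome directly or through a shared cause. The article makes the first plausible and gives figures for neither, so size and direction are unknown. The ranges above (a false benefit of 0.07 to 0.20 z, or a true -0.50 reduced to about -0.46 to -0.16, or no bias at all) rest entirely on assumed inputs and should not be read as the expected error. The t-test is unaffected. Severity: should be fixed.

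**What to change.** Delete percent attendance from the regression that estimates the intervention effect, and from the multivariable mixed model that replaces it if siblings enrol. Keep pre-randomisation covariates such as cohort and household income. Report attendance separately as an exploratory dose or mediation analysis, labelled as not estimating the effect of assignment. The Outcome measures section already plans work on mediators, although it does not name attendance, so this analysis has a natural place.

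If attendance was one of the five control variables assumed to explain 20% of the variability, restate that assumption and the power figure that depends on it.

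The cost is a line of wording, plus the power restatement if it applies. No change to design, data collection or sample size is needed, and the attendance analysis is kept.

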## Discussion

With overweight and obesity impacting the lives of at least two million boys and girls (and their families) in Canada [2,92], there is a clear need for effective interventions to promote successful pediatric weight management. This RCT builds on a solid evidence base of family-based interventions for managing pediatric obesity [89] as well as cognitive behavioral strategies to facilitate healthy changes in cognitions and lifestyle behaviors [59]. Contemporary research has demonstrated clearly that PAC interventions that are designed to manage pediatric health issues can lead to positive outcomes for both children and families [36-38], which includes a growing body of literature in the area of pediatric weight management [40-44]. This totality of evidence led us to hypothesize that children with obesity whose parents complete the CBT-based PAC intervention will achieve greater reductions in adiposity, improved lifestyle behaviours and psychosocial outcomes, and decreased cardiometabolic risk factors compared to children whose parents complete the PEP-based PAC intervention.

### Strengths and limitations

The current study has a number of noteworthy strengths. First, we took a rigorous and systematic approach to the design of this RCT as well as the development and refinement our intervention materials for parents and group leaders. The manualized intervention materials for group leaders, external expert review of intervention materials, and plan to evaluate intervention fidelity enhance methodological rigour and provide confidence that the interventions are distinct from one another, which is needed to evaluate their differential effects. Second, if the CBT and/or PEP versions of the PAC intervention help parents to make positive changes, the manualization of intervention materials enables the dissemination and evaluation of PAC in other settings (i.e., primary care, public health). Existing partnerships between our team members and health services (e.g., Alberta Health Services; http://www.albertahealthservices.ca) and non-governmental (e.g., Canadian Obesity Network; http://www.obesitynetwork.ca) organizations should facilitate the dissemination and future delivery of the PAC intervention within the province of Alberta and across Canada. Third, because most of the boys and girls enrolled in this study are recruited from the PCWH, they are almost exclusively described as *severely obese* (BMI ≥99^th^ percentile or BMI ≥40 kg/m^2^) [93]. Since much of the evidence in managing pediatric obesity includes less overweight and obese participants [89], the present RCT contributes important information regarding the impact of parent-based approaches for managing severe obesity in children. Finally, offering pediatric weight management interventions for parents exclusively represents an efficient model of care. Common sense dictates that the PAC interventions can be delivered using fewer resources (physical, human, financial) than interventions that include both parents and children. Since many pediatric weight management centers in Canada struggle to deliver health services with limited resources and infrastructure [14], interventions that are both efficient and effective are most desirable.

It is also important to acknowledge the potential limitations of this study. First, while we are implementing several retention strategies (e.g., regular telephone calls to confirm appointment and session attendance, modest incentives for families to complete outcome assessments at study time points), we know from our own clinical and research experience [48] and the published literature [94] that lack of engagement and attrition are common phenomena in pediatric weight management. These issues may have a negative impact on family recruitment and retainment within this RCT. To better understand and potentially address issues of engagement and attrition, we are currently completing an independent multi-center, qualitative study to interview 100 parents and 100 children and youth with obesity in order to understand parents’ and children’s decisions regarding engagement in and attrition from pediatric weight management centers [95]. These emerging data should help to inform decisions that should optimize recruitment and retention in the current study. Second, there is an increasing number and variety of services that relate to pediatric weight management (i.e., physical activity and exercise programs for families, community-based weight management programs, and outpatient nutrition) available to families in the Edmonton-area. Although this is advantageous from family and health services viewpoints, this reality decreases the number of local families who may be enrolled in our study. Third, our study is conducted in an outpatient clinic setting, so the health professionals performing many of the outcome assessments (e.g., anthropometry) know which families were randomized to the CBT and PEP intervention groups. Although they have no vested interest in the study as study co-investigators, this real-world environment introduces a potential source of bias (lack of assessor blinding; [52]) because all families receiving weight management care are regularly discussed during weekly case conference team meetings. Finally, to date, our discussions with families regarding a PAC approach for managing pediatric obesity have occasionally been met with resistance; since children present with the identified health concern, parents are sometimes taken by surprise with the primary role they are asked to play in the PAC intervention. Many parents embrace their leadership role in making and sustaining healthy changes within their families, although other parents will prefer that intervention efforts focus on children themselves or include both parents and children. As a consequence of these differing perspectives and intervention foci, some parents decline study participation.

The current study provides a unique opportunity by combining CBT and PAC within an intervention model to improve the health and well-being of children with obesity and their parents in a real-world, outpatient clinical setting. Findings from this research should contribute important insight into how health services can be provided effectively and efficiently to families in order to address pediatric obesity.
